## Abstract

**Background::**

To expedite the use of evidence-based smoking cessation interventions (EBSCIs) in primary care and to thereby increase the number of successful quit attempts, a referral aid was developed. This aid aims to optimize the referral to and use of EBSCIs in primary care and to increase adherence to Dutch guidelines for smoking cessation.

**Methods::**

Practice nurses (PNs) will be randomly allocated to an experimental condition or control condition, and will then recruit smoking patients who show a willingness to quit smoking within six months. PNs allocated to the experimental condition will provide smoking cessation guidance in accordance with the referral aid. Patients from both conditions will receive questionnaires at baseline and after six months. Cessation effectiveness will be tested via multilevel logistic regression analyses. Multiple imputations as well as intention to treat analysis will be performed. Intervention appreciation and level of informed decision-making will be compared using analysis of (co)variance. Predictors for appreciation and informed decision-making will be assessed using multiple linear regression analysis and/or structural equation modeling. Finally, a cost-effectiveness study will be conducted.

**Discussion::**

This paper describes the study design for the development and evaluation of an information and decision tool to support PNs in their guidance of smoking patients and their referral to EBSCIs. The study aims to provide insight into the (cost) effectiveness of an intervention aimed at expediting the use of EBSCIs in primary care.

## Introduction

Smoking remains the highest contributor to substance-attributable mortality (Peacock *et al.*, 2018). In the Netherlands, around 20,000 people die from firsthand or secondhand smoke inhalation each year (CBS, 2018). Consequently, in 2018, the Dutch government created the National Prevention Act which, among other things, aims to create a smoke-free generation in 2040 (Nationaal Preventieakkoord, 2018). In 2018, 36.9% of Dutch smokers attempted to quit (Bommele and Willemsen, 2019). However, only 5% of those who quit remain abstinent after 12 months (Fiore *et al.*, 2000; Hughes *et al.*, 2004).

The use of an evidence-based smoking cessation intervention (EBSCI) can double the chance of successful smoking cessation after 12 months (West *et al.*, 2015). EBSCIs come in two forms: behavioral counseling and supplementations. Behavioral counseling can consist of face-to-face counseling by a healthcare professional (HCP) such as a general practitioner (GP) or a practice nurse (PN) or trained stop coach outside the GP setting (Pieterse *et al.*, 2001; Aveyard *et al.*, 2012; Stead *et al.*, 2013; Verbiest *et al.*, 2013; Papadakis *et al.*, 2016; van Rossem *et al.*, 2017), tailored online counseling (eHealth) (Te Poel *et al.*, 2009; Stanczyk *et al.*, 2014), telephone counseling (Berndt *et al.*, 2016), and group counseling (McEwen *et al.*, 2006). However, only 25%–30% of smokers report using behavioral counseling methods (Borland *et al.*, 2012; Filippidis *et al.*, 2019). The effectiveness of behavioral counseling can be increased through supplementation with nicotine replacement therapy such as nicotine gum or patches (available over the counter at pharmacies, drugstores, and large supermarkets) (Stead *et al.*, 2012) or pharmacotherapy (Hurt *et al.*, 1997; Hughes *et al.*, 2005; Tonstad *et al.*, 2006) of which the latter can only be prescribed in the Netherlands via the GP setting to patients indicating that they are willing to make use of them (Chavannes *et al.*, 2017).

The general practice setting is a gateway to reach and advise smokers; most Dutch smokers visit their GP yearly (Boerdam and Bevolkingstrends, 2016) and smokers have a high level of trust in their GP (Guassora and Gannik, 2010). Theoretically, a good fit between the treatment and the patient’s needs and preferences improves the patient’s chances of successfully quitting smoking. Discussing intervention options, their characteristics and a subsequent referral to cost-effective EBSCIs, such as eHealth interventions (Cheung *et al.*, 2017; 2018) can assist smokers in finding the best way to quit in accordance with their needs, while also lowering the time burden of smoking cessation counseling during (chronic care) consultations.

The Dutch smoking cessation guidelines for general practices instruct HCPs to actively offer smokers cessation treatment and to refer smokers to EBSCIs that fit patients’ needs and preferences (Chavannes *et al.*, 2017). Up till 10 years ago, smoking cessation support was predominantly provided by the GP. Nowadays, in most Dutch practices, smoking patients are referred to a PN (Dierick-van Daele *et al.*, 2009). PNs are specialized in chronic care (Heiligers *et al.*, 2012), which mostly consists of lifestyle change guidance. GPs and PNs usually use an evidence-based health counseling protocol similar to the 5-A’s (Ask, Advise, Assess, Assist, and Arrange) Tobacco Cessation Guideline (Fiore *et al.*, 2000) as also prescribed by the Dutch smoking cessation guidelines (Chavannes *et al.*, 2017) and previous studies in the GP setting (Pieterse *et al.*, 2001; de Ruijter *et al.*, 2016).

However, PNs’ adherence to smoking cessation guidelines and the referral of patients to fitting EBSCIs is sub-optimal (Cabana *et al.*, 1999; de Ruijter *et al.*, 2017). This may result from PNs unfamiliarity with EBSCIs, which hinders them in confidently discussing options with patients (de Ruijter *et al.*, 2017). Other barriers may be a high workload, a shortage of resources, or an unfavorable perception of the usability of cessation guidelines (Abrahamson *et al.*, 2012; de Ruijter *et al.*, 2017).

In order to expedite the use of EBSCIs in primary care and to thereby increase the number of successful quit attempts, a referral aid was developed. This aid aims to optimize the referral to and use of EBSCIs in primary care and to increase adherence to Dutch guidelines for smoking cessation. This paper aims to describe the development of the referral aid, as well as the design of the associated effectiveness and cost-effectiveness studies.

## Method

### Ethical approval

The medical ethics committee of the University Hospital Maastricht and Maastricht University evaluated the research proposal and indicated that no medical ethical clearance for this study was needed according to the rules of the Medical Research Involving Human Subjects Act (WMO – 2018-1038). The study was registered at the Netherlands Trial Register (NL7020, https://www.trialregister.nl/trial/7020).

### Study design

The aim is to conduct a multi-site two-group parallel randomized controlled trial involving an experimental condition and a control condition. Patients in the control condition will receive care as usual, which usually includes at least a mandatory brief smoking cessation advice and can be supplemented with counseling based on an evidence-based health counseling protocol similar to 5-A’s(Ask, Advise, Assess, Assist, and Arrange) Tobacco Cessation Guideline (Fiore *et al.*, 2000) as also described in the Dutch guidelines for smoking cessation (Chavannes *et al.*, 2017) and previous studies in the GP setting (Pieterse *et al.*, 2001; de Ruijter *et al.*, 2016) in the way the individual PN sees fit. In addition to the usual care, patients in the experimental condition will receive guidance and referral by the PN in accordance with the referral aid in order to select an EBSCI that fits their needs and preferences, which acts as an expansion on the Assist and Arrange steps from the 5-A’s protocol (Fiore *et al.*, 2000). The chosen EBSCI can either be administered by the PN (i.e., face-to-face counseling) or coordinated by the PN (e.g., eHealth, telephone counseling).

Randomization will occur on a practice level to prevent bias between the PN level or the patients level. General practices will be randomly allocated to either the control condition or the experimental condition in a 1:1 ratio. Randomization will take place via a random number generator that creates a string of numbers (1 = control condition, 2 = experimental condition), which will be allocated to general practices in order of registration. Patients are allocated based on their GP practice allocation. By allocation on the practice level, PNs cannot accidentally bias patients from the control group with information intended for the experimental group. As PNs from the experimental condition are provided with an intervention and PNs from the control condition are only asked to provide care as usual, blinding of the PNs is impossible. Patients will be semi-blinded, as they are unaware of the procedure of any other group than the one they attend.

Patients have to answer two questionnaires – at baseline and follow-up. This can be done on paper or online. Patients receive a link to the questionnaire or a paper version after they have been registered by the PN. The follow-up measurement will take place six months after the baseline questionnaire has been answered. The study design is illustrated in Figure 1.

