### Recruitment of practice nurses

From January 2019 until May 2020, PNs in the Netherlands will be approached to participate in the study. The task of the PNs will be twofold – recruiting smokers and referral to EBSCIs in accordance with the intervention’s method.

An information package including a study invitation letter and an intervention summary will be sent to general practices spread over the Netherlands. Dutch primary care associations who support the study will also distribute the information letters to their associate general practices through their own communication channels. To gauge the interest in participating in the study, approached practices will be contacted via telephone after two weeks. HCPs expressing an interest in participating will be sent a more detailed guideline for the study and will be asked to sign a study participation form. PNs are requested to recruit 10–20 patients each. To prevent attrition and stimulate active recruitment by the PNs, participating PNs who recruit at least five patients will receive a remuneration of €100. Inclusion criteria will be that PNs are employed by one or more general practices in the Netherlands and they indicate that they provide smoking cessation counseling as such.

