### Recruitment of smokers

From May 2019 until May 2020, participating PNs are requested to inquire about the smoking status of all their patients with smoking-related complaints. Patients who report to be a smoker (no set minimum requirements) will be asked to participate in the study. If they agree to participate, they will receive brief guidance and referral advice dependent on the condition in which the PN has been assigned. Written informed consent will be obtained from all participants. Smokers will be rewarded a gift voucher of €10 for participating if they answer both questionnaires.

Inclusion criteria will be that patients smoke tobacco products, are at least 18 years old, and able to read and understand Dutch. Patients who only use e-cigarettes/e-cigars are not eligible to participate.

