## Discussion

### Potential strengths of the study

The first potential strength of the study is the use of a random allocation of PNs via a computer algorithm to mitigate possible biases within general practice settings as PNs working within the same general practice setting, but allocated to different conditions may have an impact on the implementation of the study. Second, the intervention was pilot tested among a group of potential users, both PNs and smokers, and experts from the field to test the usability and to remove ambiguities. Third, the GP setting was used as a gateway to reach the target group as most smokers visit their general practice yearly (Boerdam and Bevolkingstrends, 2016) and have a high level of trust in their GP (Guassora and Gannik, 2010), which makes it more accessible than specialty centers at the hospital level. Fourth, the intervention consists of a summary of various already proven effective smoking cessation methods, which are often underused at the moment. This study may help to increase their uptake. Fifth, a cost-effectiveness study will be performed, which will provide an estimation of the additional costs and benefits of the intervention as compared to care as usual. Sixth, in order to take into account, the potential of low health literacy of patients, the materials have been written in a clear and comprehensible language in accordance with the applicable Dutch guidelines. Lastly, using the intervention takes hardly any additional time, making it a perfect fit in the timeslots of their usual consultation sessions. This makes it easier for PNs to participate in the study.

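### Allocating practices independently does not keep a practice nurse who works in two participating practices within one condition, and the article names two different units of allocation

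*Protocol article*

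**What the plan says.** Under Study design, the unit is the practice: "General practices will be randomly allocated to either the control condition or the experimental condition in a 1:1 ratio". The numbers come from a random string "which will be allocated to general practices in order of registration", and for patients the rule is: "Patients are allocated based on their GP practice allocation". The section then states the benefit without qualification: "By allocation on the practice level, PNs cannot accidentally bias patients from the control group with information intended for the experimental group".

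Three other places make the PN the unit:

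- Abstract, Methods: "Practice nurses (PNs) will be randomly allocated to an experimental condition or control condition".
- Recruitment of smokers: the care a patient receives is "dependent on the condition in which the PN has been assigned".
- Discussion, Potential strengths: the article counts as a strength "the use of a random allocation of PNs via a computer algorithm".

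Under Recruitment of practice nurses, the inclusion criterion is that "PNs are employed by one or more general practices in the Netherlands" and provide cessation counselling.

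The Sample size section nests patients in general practices with five per cluster. It reaches that figure from 60 PNs recruiting 10 patients each with half lost, so one PN stands for one practice.

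**The concern.** The intervention is largely knowledge and a way of counselling that the PN carries into the consultation, so the PN is the channel through which control patients could receive it. Allocation by practice closes that channel only if each PN belongs to one allocated unit. The eligibility rule does not require this, and the article gives no rule for two practices that share a PN.

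For a PN whose practices fall in different conditions, the article's rules also conflict. Study design gives the patient the practice's condition, while Recruitment of smokers gives the patient the PN's condition, which is undefined for that PN. Website access to the manual likewise depends on the PN's condition.

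At stake are dilution of the treatment contrast, with a loss of power, and an unclear cluster for the multilevel models.

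**Working it through.** **1. The plan's own sample size.** Inputs from the Sample size section: 5% versus 15%, odds ratio 0.30, alpha 0.05 (taken as two-sided; the article does not say), power 0.80, cluster size 5, ICC 0.01.

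- The pooled two-proportion formula is n per arm = [1.96·√(2·p̄·(1−p̄)) + 0.842·√(p₁(1−p₁)+p₂(1−p₂))]² / (p₂−p₁)². With p̄ = 0.10 this is (0.8316 + 0.3521)² / 0.01 = 140.1, so 141 per arm and 282 in total. Using the rounded odds ratio of 0.30 gives 284, within 3% of the stated 292.
- The design effect is 1 + (5−1)·0.01 = 1.04. Then 292·1.04 = 303.7, so 304, and 282·1.04 = 293.3, so 294. The stated 300 lies between them.

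The sample size is therefore reproduced and is not in dispute.

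**2. Chance that one PN holds both conditions.** With k participating practices, each allocated independently 1:1, the probability is 1 − 2·(1/2)^k. This gives 0.50 for k = 2 and 0.75 for k = 3. If the string forced equal arms over 60 practices, the figure for k = 2 would be 30/59 = 0.51, practically the same.

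**3. Consequence for power (assumption-based).** The article does not give the share g of PNs with more than one participating practice. Three assumptions are made:

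- each such PN has exactly two participating practices, with similar patient numbers across PNs and practices;
- half of these PNs are discordant, so a fraction f = g/2 of control patients is seen by a PN who holds the aid;
- those patients gain the full 10-point effect, which is an upper bound.

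The control rate becomes 5% + f·10 points. The effective size is 150/1.04 = 144.2 per arm. Power is Φ{[(p₂−p₁)·√144.2 − 1.96·√(2·p̄·(1−p̄))] / √(p₁(1−p₁)+p₂(1−p₂))}. Without contamination this is Φ[(1.2010 − 0.8316)/0.4183] = Φ(0.883) = 0.811.

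| g | f | Control rate | Power at 300 | N for 80% power |
|---|---|---|---|---|
| 0 | 0 | 5.0% | 81% | 294 |
| 10% | 5% | 5.5% | 76% | 331 |
| 20% | 10% | 6.0% | 71% | 377 |
| 30% | 15% | 6.5% | 65% | 433 |

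**4. Effect on standard errors.** If every cluster were really a linked pair of 10 patients, the design effect would be 1 + 9·0.01 = 1.09. Then √(1.09/1.04) = 1.024, so standard errors would rise by about 2.4%.

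**The case against.** The eligibility sentence concerns employment. It does not say that more than one of a PN's practices would enrol, and the planning figures assume one PN per practice. Study design is explicit that practices are randomised. The Discussion sentence goes on to explain that the aim was to avoid PNs in one practice being in different conditions, which is the rationale for practice-level allocation. The PN wording elsewhere can thus be read as shorthand for PNs inheriting their practice's condition. A rule for shared PNs might also sit in a full protocol that is not shown.

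Much of this stands. The route is possible but not shown to have occurred, and the absence of an operational rule from an article would not by itself be a fault. What remains is that the article makes a categorical claim that its own eligibility and allocation rules do not support, and that its sections disagree on the unit.

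A reader might infer that the protection fails for the trial as a whole. It does not: for a PN with one participating practice it holds. A reader might also infer that standard errors are seriously wrong. At the planned ICC of 0.01 the difference is about 2.4%, even if every cluster were a linked pair.

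**Conclusion.** The point holds within limits. As written, the allocation rule can place one PN in both conditions, so the unqualified claim of no contamination does not follow for PNs with two or more participating practices. For two-practice PNs the chance is 50%.

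The loss of power cannot be established from the article, because the number of such PNs is not given. The range of about 76% to 65% rests on assumed shares of 10% to 30%, two practices per such PN and full transfer of the effect. It shows sensitivity and is not an estimate. A reader might take these figures as the trial's actual power, which the article does not support. Planned power is only 81%, so there is little slack, and any such contamination would tend to pull the result towards no difference.

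The inconsistent unit of allocation needs correcting whatever that number turns out to be.

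**What to change.** **Allocation.** Under Study design, state that participating practices sharing a PN receive a single allocation. Use that linked unit as the cluster in the multilevel models.

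**Wording.** Name the same unit in the Abstract, Recruitment of smokers, Sample size and Discussion. Limit the contamination statement to PNs who serve one allocation unit.

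**Practices already allocated.** Do not let a PN choose one practice to recruit from once allocation is known: that invites selection, and contamination remains if the PN already holds the manual. Keep all patients as randomised in the primary analysis. Report how many PNs, and how many of their patients, have discordant practices. Add a sensitivity analysis that excludes the patients of those PNs in both conditions.

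**Cost.** One registration question, one allocation rule, and slightly fewer, larger clusters. The Limitations section already reports slow recruitment in the past tense, so the allocation rule may come too late for part of the sample. The count, the sensitivity analysis and the wording changes remain possible regardless.

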**Figure 1. f1:**
[figure not shown]
Flowchart of the study design

### Recruitment of practice nurses

From January 2019 until May 2020, PNs in the Netherlands will be approached to participate in the study. The task of the PNs will be twofold – recruiting smokers and referral to EBSCIs in accordance with the intervention’s method.

An information package including a study invitation letter and an intervention summary will be sent to general practices spread over the Netherlands. Dutch primary care associations who support the study will also distribute the information letters to their associate general practices through their own communication channels. To gauge the interest in participating in the study, approached practices will be contacted via telephone after two weeks. HCPs expressing an interest in participating will be sent a more detailed guideline for the study and will be asked to sign a study participation form. PNs are requested to recruit 10–20 patients each. To prevent attrition and stimulate active recruitment by the PNs, participating PNs who recruit at least five patients will receive a remuneration of €100. Inclusion criteria will be that PNs are employed by one or more general practices in the Netherlands and they indicate that they provide smoking cessation counseling as such.

### Recruitment of smokers

From May 2019 until May 2020, participating PNs are requested to inquire about the smoking status of all their patients with smoking-related complaints. Patients who report to be a smoker (no set minimum requirements) will be asked to participate in the study. If they agree to participate, they will receive brief guidance and referral advice dependent on the condition in which the PN has been assigned. Written informed consent will be obtained from all participants. Smokers will be rewarded a gift voucher of €10 for participating if they answer both questionnaires.

Inclusion criteria will be that patients smoke tobacco products, are at least 18 years old, and able to read and understand Dutch. Patients who only use e-cigarettes/e-cigars are not eligible to participate.

### Intervention: the referral aid

The referral aid is named ‘StopWijzer’, which can be translated as either stop guide or stop wiser. The content of the referral aid is based on a needs assessment consisting of a literature review (e.g., Stanczyk et al., 2014; De Vries, 2017; de Ruijter *et al.*, 2018), individual semi-structured interviews among GPs (*n* = 5), PNs (*n* = 20), and smokers (*n* = 9), a Delphi study on the referral to EBSCIs (not published yet) and the input of an advisory board consisting of experts representing various Dutch smoking cessation-related organizations of whom six were actively involved

The PNs in the experimental condition will receive an intervention manual to aid them in discussing smoking cessation with their patients and to help them select an EBSCI that fits the patient’s needs and preferences. Smoking cessation interventions that are included in the referral aid are: (1) face-to-face counseling (Pieterse *et al.*, 2001); (2) counseling via the Internet (eHealth) (Te Poel *et al.*, 2009; Stanczyk *et al.*, 2014); (3) telephone counseling (Berndt *et al.*, 2016); (4) group counseling (McEwen *et al.*, 2006); (5) pharmacotherapy; and (6) nicotine replacement therapy. It is strongly recommended to only offer pharmacotherapy and nicotine replacement therapy in combination with a form of behavioral counseling, as it is also counseled by the Dutch smoking cessation guidelines (Chavannes *et al.*, 2017).

The use of nonevidence-based methods such as acupuncture and the use of e-cigarettes are also discussed in the referral aid as smokers might inquire about the effectiveness of these methods. The referral aid actively encourages PNs to not recommend these methods and stimulates them to advance the aforementioned EBSCIs as suitable alternatives.

The PN starts with inquiring about the patients’ smoking habits and his or her interest in undertaking a smoking cessation attempt. They also inform the patient about the referral aid and the underlying study (see also Figure 2).

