**Figure 2. f2:**
[figure not shown]
Flowchart referral aid

Patients who agree to participate in the study will be counseled in accordance with the referral aid. First, the PN inquires about earlier cessation attempts and smoking cessation methods patients may have used during these attempts. Second, the PN informs the patient about the available EBSCIs and their advantages and disadvantages based on the information provided in the intervention’s manual. If necessary, the manual also allows PNs to provide information on possible reimbursements by health insurers. Third, the PN and patient discuss which EBSCI best fits the patient’s needs and preferences. Fourth, the smoker selects an EBSCI and chooses a cessation date. Lastly, depending on the EBSCI chosen by the patient, PNs schedule at least one follow-up appointment in two–five weeks, in order to evaluate and, if necessary, to select another EBSCI.

If the smoker is not (yet) interested in participating, PNs are advised to give the smoker a flyer to take home. This flyer contains information about participating in the study and a summary of the different EBSCIs. This way, smokers may be stimulated to consider smoking cessation at a later point in time. If the smoker is uncertain about participating, PNs are advised to, in addition to handing out the aforementioned flyer, schedule a follow-up meeting or telephone call with the smoker for further discussion on participation in the study.

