#### Promotion materials

In addition, the package also will contain a stack of business cards with the contact information of the research team and a link to the project’s website. Also enclosed will be a poster, which is used to promote the project in the practice’s waiting room. A digital version of the poster that can be displayed on waiting room screens will be sent via email. Lastly, a pen and a notebook featuring the project’s logo will be included as a small reminder.

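### Intervention contact before agreement is described only for the referral-aid arm, and the article does not say that recruitment is the same in control practices

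*Protocol article*

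**What the plan says.** **Order of allocation and recruitment.** Under Study design, practices are randomised 1:1 in order of registration and patients follow: "Patients are allocated based on their GP practice allocation". The same section states that "blinding of the PNs is impossible". Recruitment of smokers gives one sequence for both arms: "If they agree to participate, they will receive brief guidance and referral advice dependent on the condition in which the PN has been assigned".

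**Before agreement, referral-aid arm.** In Intervention: the referral aid, the PN opens by asking about smoking habits and interest in quitting, and then: "They also inform the patient about the referral aid and the underlying study". The text after Figure 2 turns to patients who agree only after this. A smoker who is not yet interested is handed a flyer: "This flyer contains information about participating in the study and a summary of the different EBSCIs". The stated purpose is to prompt thought about quitting later. For an uncertain smoker the PN should in addition "schedule a follow-up meeting or telephone call with the smoker for further discussion on participation in the study".

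**Materials.** The flyer and the promotion items stand under Intervention materials. Of the poster the article says: "Also enclosed will be a poster, which is used to promote the project". Neither the Flyers nor the Promotion materials text names an arm. The Website section puts the digital flyer among the items open to experimental PNs and limits control smokers to the general part of the site.

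**Control arm.** Study design says that "PNs from the control condition are only asked to provide care as usual". No recruitment path specific to control practices is described.

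**What is acknowledged.** Potential limitations admits that PNs may favour smokers already willing to stop. It does not say that this could differ by arm. The remedy it names is the manual and the flowchart handout, and Intervention: the referral aid gives the manual to PNs in the experimental condition.

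**The concern.** Randomising practices balances practices. It does not balance the patients who later consent, when recruiters know the arm and the information given before consent can depend on it. As written, some tools that bring patients into the study also carry intervention content. This differs from the selection the article acknowledges, which concerns whom the nurse invites. Here the patient's own decision to join may be made on different information, and some enrolled patients may already have received the EBSCI summary.

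If so, the arms can differ in readiness to quit for reasons unrelated to what the aid does for enrolled patients. The odds ratio for 7-day abstinence and the cost per additional quitter would absorb that difference. Baseline adjustment cannot be relied on to remove it: the section on prompts lets smokers fill in the paper questionnaire directly after the PN meeting, so baseline motivation and intention may already reflect the contact.

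**Working it through.** **1. What each arm is described as getting before agreement**

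| Element | Referral-aid arm | Control arm |
|---|---|---|
| Information about the study | Yes | Yes, implied: patients are asked to take part and give written consent |
| Explanation of the aid | Yes | Not described; patients are said to be unaware of the other group's procedure |
| Flyer with EBSCI summary | Yes, if not yet interested or uncertain | Not described; digital copy listed for experimental PNs only |
| Second contact about participation | Yes, if uncertain | Not stated either way |
| Poster | In the package; arm not named | Not stated either way |
| EBSCI counselling, choice of method, quit date | After agreement | Not part of the control condition |

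The difference is well supported for the explanation of the aid, fairly well for the flyer, and open for the poster and the second contact.

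**2. The plan's own figures**

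Inputs from Sample size: 5% against 15%, power .80, alpha .05 (sides not stated), cluster size 5, ICC .01, N = 292 before and 300 after clustering.

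- Two-sided two-proportion formula: 141 per arm, 282 in total. With an odds ratio of 0.30 applied to 15% (5.03% against 15%): 284, within 3% of 292.
- Design effect: 1 + (5 - 1) × .01 = 1.04. 292 × 1.04 = 304, against the stated 300.
- Effective n per arm at 300: 150 / 1.04 = 144.2. Power at 5% against 15%: .811.

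The stated sample size is consistent with its inputs, and this point does not depend on it.

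**3. Illustration of what a difference in recruits could do**

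The documents give no figure for this, so both inputs are assumptions. A share *s* of experimental patients enters only through extra routes and would quit at rate *r* without any effect of the aid; all others quit at 5%.

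False difference = s × (r - 5%). The chance of a two-sided significant result under no true effect uses the normal approximation with 144.2 effective patients per arm.

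| s | r | False difference (points) | Chance of significance |
|---|---|---|---|
| 30% | 2% | .30 × (-3) = -0.9 | .065 |
| 10% | 10% | .10 × 5 = +0.5 | .054 |
| 20% | 15% | .20 × 10 = +2.0 | .110 |
| 30% | 15% | .30 × 10 = +3.0 | .178 |
| 30% | 20% | .30 × 15 = +4.5 | .313 |

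The reference value is .05. At r = 2% the false difference goes against the intervention.

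**4. Patient numbers**

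If extra routes moved the patient split to 180:120 (experimental to control, also an assumption), power would fall from .811 to .781. That is a minor loss.

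**The case against.** **The stronger reading.** A reader might infer that control practices have no poster, no flyer and no way back for smokers who first decline. The documents do not support that. The Flyers and Promotion materials texts name no arm. Nothing in Recruitment of smokers bars a control PN from asking again. The remark that control PNs only provide usual care explains why blinding is impossible; it is not a recruitment rule and cannot be literal, since those PNs also invite and register patients. Data analysis plans to compare appreciation of the materials between conditions, which sits badly with control patients seeing none. This objection stands, and the claim is limited accordingly.

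**A condensed article.** A control recruitment script may well exist in the full protocol or in the study guideline sent to interested practices. Its absence here is therefore no finding in itself. What remains is what the article does state: in the referral-aid arm, intervention content is tied to the recruitment step.

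**Thin exposure.** Advantages and disadvantages of the EBSCIs, the choice of method and the quit date all follow agreement. Telling patients what they are joining is part of consent. The flyer and second contact reach only those who do not agree at once. This stands: prior exposure is partial.

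**Size and direction.** The larger probabilities above need s of at least 20% and r of at least 15%. An r of 20% without the aid exceeds the 15% the plan expects with it. Smokers who first declined could be less ready to quit, and anyone who quit on the flyer alone would no longer be eligible and would not be counted; both work against the intervention. This stands too: no direction can be claimed.

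**Partial cover.** Motivation, time frame for quitting and dependence are measured at baseline, so differences can be examined, subject to the timing problem already noted.

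**Conclusion.** The point holds in limited form. Unblinded PNs recruit after practice allocation. The article describes explanation of the aid, an EBSCI flyer and a second contact before agreement for the referral-aid arm only, and does not say that control recruitment is the same. Consent and prior knowledge can therefore differ by arm.

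The flyer is a problem on either reading. If only experimental practices use it, recruitment differs by arm. If control practices use it too, control smokers receive intervention content. The named remedy for selection bias does not settle the matter, since the manual is described for experimental PNs.

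No bias has been demonstrated. The range of -0.9 to +4.5 points and the rejection probabilities from .054 to .313 rest wholly on assumed values of s and r, with 150 patients per arm, a design effect of 1.04 and a 5% quit rate. They show only that, at so low a control rate, modest differences in who enrols can matter. This is a worthwhile, inexpensive improvement to the design, not a fatal flaw.

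**What to change.** 1. Until written consent, use the same recruitment pack in both conditions: the same study information, the same project poster, a study flyer without the EBSCI summary, and the same rule for recontacting undecided smokers.
2. Give the detailed explanation of the aid and the EBSCI flyer only after consent, in experimental practices.
3. Add an entry-route field to the website registration (first visit, returned after flyer, recontacted, poster) and report it by arm.
4. Reconcile Recruitment of smokers, Intervention: the referral aid (with the text after Figure 2), Flyers, Promotion materials and Website, so that each item is assigned to one or both arms and placed before or after consent. If control practices already have the poster and the same recontact rule, one sentence settles that part.

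**Cost.** A reprint of the flyer and poster, and a mailing. With 60 PNs allocated 1:1 and one PN per practice, that is about 30 control practices, plus replacement flyers for the others. One extra registration field; no extra patients or staff. The real downside is that decliners in experimental practices no longer receive the EBSCI summary from the study, which the article offers deliberately to prompt later quitting.

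Where recruitment has already taken place, what remains possible is to state which items control practices had and to report any recorded entry routes and baseline readiness by arm.
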